#### Participant timeline {13}

#### Sample size {14}

##### *Clinical*

The sample size used in this study is based on simulation models described in *Hayes and Bennet* et al. for incidence rates [50]. Routine data collected from all health facilities in Nyimba district in Zambia estimated an incidence rate of 0.312 cases per person from January to June 2019. Using these estimates in Eq. 1 [50], we estimated that in order to detect a reduction of 35% on malaria incidence, with 80% power at the 5% significance level, 338 houses were required per study arm when following one child per household per year [51]. A total of 400 households with one child each were recruited per treatment arm. The additional households were enrolled to account for households lost to follow-up.

Data collected from all health facilities in Chokwe district, Mozambique, estimated an incidence rate of 0.325 cases per person from January to June. Using the same formula, we estimated that 324 children were required per treatment arm to observe a 35% treatment effect with 80% power at the 5% significance level [50]. A total of 400 households were also recruited in Mozambique.
1$$ \mathrm{y}={\left({\mathrm{z}}_{\upalpha /2}+{\mathrm{z}}_{\upbeta}\right)}^2\left({\uplambda}_0+{\uplambda}_1\right)/{\left({\uplambda}_0\hbox{-} {\uplambda}_1\right)}^2 $$

##### *Entomological*

House screening is projected to reduce indoor malaria vector collections by at least 50% [51]. We used the *Hayes and* Bennet model for sample size calculation when using means to determine the number of households required to demonstrate a 50% reduction of indoor-entering mosquitoes associated with house screening, with 80% power at the 5% level of significance [50]. A study assessing different mosquito sampling schemes using light traps and human biting catches in Nyimba district, Zambia, in 2014, estimated that 2.6 *An. funestus* were caught using CDC light traps per night [52]. Using Eq. 2 below, we estimated that we would require 17 houses in each arm of the study. An additional 12 households were recruited for mosquito sampling to make a total of 30 households per study arm to allow for sampling of mosquitoes using both the CDC LTs and PSC techniques. Each sampling technique was used to sample mosquitoes from 15 households per study arm. As the standard deviation (SD) for this data was not reported, we assumed a SD of 1.96 for the sample size calculation.

Mosquito data from Chokwe in Mozambique was not available, and there we used the same sample size as that of Zambia of 30 households per treatment arm.
2$$ \mathrm{n}={\left({\mathrm{z}}_{\upalpha /2}+{\mathrm{z}}_{\upbeta}\right)}^2\left({\sigma_0}^2+{\sigma_1}^2\right)/{\left({\upmu}_0\hbox{-} {\upmu}_1\right)}^2 $$

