#### Trial design {8}

This study is a multicounty, two-armed household randomized controlled trial using a generalized randomized block design, with the village as the block. Prior to the selection of the study households in each of the three study locations in the three countries, a baseline household census will be conducted in each village in the target areas. A database of study households that meet the eligibility criteria will then be generated.

During the household census, household access to LLINs will be assessed to ensure that there is an LLIN for every sleeping place in the enumerated household, assuming two people use a single net. House type and potential mosquito entry points for each enumerated household will also be recorded. If the household does not have an LLIN for every sleeping space, this will be issued during the baseline household socio-demographic survey that will be conducted after the household census. The socio-demographic survey will be conducted in 800 randomly selected study households. After the baseline socio-demographic survey, one child between 6 months and 13 years will be randomly selected from the 800 study households to be included in the study cohort. This study cohort will then be screened for malaria parasites (parasitological survey) at the beginning and end of the transmission season. Sentinel households, 120, will be selected from the enrolled study households for an entomological sampling of adult mosquitoes. Exposure to indoor mosquito bites will be estimated by routine surveillance of the sentinel households using CDC light traps and while indoor mosquito resting densities will be estimated using Pyrethrum Spray Catch (PSC) technique. Three months prior to the start of the transmission season (January-May), 400 enrolled households will be randomized to the intervention arm and all mosquito entry points (windows, eaves and doors) screened.

The remaining 400 households will be assigned to the control (no-screening) arm. Households lost to follow-up will be replaced with non-randomized households enumerated during the household census.

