##### *Entomological endpoints*

The primary entomological endpoint will be the relative indoor mosquito density, expressed as the average number of mosquitoes caught per trap night in each study arm. The secondary endpoint will be the entomological inoculation rate (EIR) incorporating the blood meal source (human biting rate) and the mosquito sporozoite positivity per study arm.

A total of 30 sentinel houses per study arm (*N*=60) per country will be randomly selected for adult mosquito collections. The household selection will be stratified by village and geographical area so that an equal number of sentinel houses are selected in each village and equally spread over the study area. This stratified randomization by the village will reduce the likelihood of imbalances between study arms. Indoor host-seeking mosquitoes will be collected for 5 days each month using CDC UV light traps from 15 sentinel households. The CDC light trap will be placed next to the sleeping space of the study enrolled child and will be raised 1.5 m from the ground. The light trap will be set up at 7:00 p.m. and mosquitoes collected at 7:00 a.m. the next morning.

Indoor resting mosquitoes will be collected using pyrethrum spray catches (PSC) in the remaining 15 sentinel households in each arm of the study. The collections will be done inside the room where the child recruited into the study cohort sleeps. Mosquito sampling using PSC will be conducted early in the morning between 06:00 and 08:00 h. All the exit points to the sleeping area will be shut and a white sheet spread on the floor. An insecticide will then be sprayed in the room to knock down mosquitoes which will then be collected after 10 min. This sampling will be conducted 1 day for each month in the fixed sentinel households throughout the study period.

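### The 17 houses per arm for mosquito sampling do not follow from the protocol's own Eq. 2 (36 with equal SDs), and with 15 light-trap houses per arm the calculation shown does not support 80% power

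*Protocol article*

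**What the plan says.** Under Sample size {14}, Entomological, the protocol article sizes the mosquito collections to show a halving of indoor-entering mosquitoes "with 80% power at the 5% level of significance". The control mean comes from an earlier survey in Nyimba, which "estimated that 2.6 *An. funestus* were caught using CDC light traps per night". That survey reported no SD, so the authors say openly that they assumed 1.96. Eq. 2 is the usual two-means formula, with the sum of the two arm variances in the numerator. The result is given as: "Using Eq. 2 below, we estimated that we would require 17 houses in each arm of the study".

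The text continues: "An additional 12 households were recruited for mosquito sampling to make a total of 30 households per study arm". The 30 are then divided between light traps and pyrethrum spray catches: "Each sampling technique was used to sample mosquitoes from 15 households per study arm". The same 30 per arm are used for Mozambique because no local data were available.

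Outcomes {12}, Entomological endpoints, repeats the split. On light traps it says: "Indoor host-seeking mosquitoes will be collected for 5 days each month using CDC UV light traps from 15 sentinel households". Spray catches go to the other 15 houses in each arm, one day a month, and the total is 60 sentinel houses per country. Trial design {8} gives a different count: "Sentinel households, 120, will be selected from the enrolled study households".

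**The concern.** All the inputs to Eq. 2 are printed beside it, so a reader can redo the sum, and it does not give 17. The figure is about half of what the formula returns when the one stated SD is used in both arms. The design then falls short even of 17, because the 30 houses per arm are shared between two techniques and the light-trap comparison, which is what was sized, has 15.

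Indoor density is the primary entomological endpoint, and the Discussion promises high-quality entomological evidence for policy. A reader who takes the 80% at face value would judge a non-significant light-trap result against a power figure that the printed calculation does not justify. The trial's main endpoint, clinical malaria incidence, is sized separately with Eq. 1 and is not affected.

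**Working it through.** **Inputs** (all from Sample size {14}, Entomological, unless noted)
- Control mean μ0 = 2.6 per trap-night; a 50% reduction gives μ1 = 1.3 and a difference of 1.3.
- SD = 1.96, one value, with no separate SD for screened houses. 1.96² = 3.8416.
- 80% power and 5% level, two-sided because Eq. 2 uses z for α/2: (1.960 + 0.8416)² = 7.849.
- Light-trap houses: 15 per arm (also in Entomological endpoints).

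**Trying to reproduce 17**
- Eq. 2 as printed, same SD in both arms: 7.849 × (3.8416 + 3.8416) / 1.69 = 35.68, so 36. This is not 17.
- One variance only: 7.849 × 3.8416 / 1.69 = 17.84. Truncated, this is 17.
- Eq. 1 appears to be truncated too. With (1.96 + 0.84)² = 7.84, it gives 338.46 for Zambia and 324.92 for Mozambique, printed as 338 and 324.
- 17 + 12 = 29, not 30, whereas 18 + 12 = 30. So 17.84 may have been rounded up in one place and truncated in another.

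**How far 36 depends on equal SDs**

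| Assumption for screened houses | Eq. 2 result | Houses per arm |
|---|---|---|
| SD 1.96 (same as control) | 35.68 | 36 |
| Variance proportional to mean (1.9208) | 26.76 | 27 |
| SD proportional to mean (0.98) | 22.30 | 23 |
| Zero variance (lower limit) | 17.84 | 18 |

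With a control SD of 1.96 and a two-sided test, no choice for the screened arm brings the requirement down to 17.

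**Power on the protocol's basis, one value per house**

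Power = Φ(1.3 / √((σ0² + σ1²)/n) − 1.96).
- n = 15, equal SDs: 1.3 / √(7.6832/15) = 1.3 / 0.7157 = 1.816; Φ(−0.144) = 44%.
- n = 15, variance proportional to mean: 1.3 / √(5.7624/15) = 2.097; Φ(0.137) = 56% (0.555).
- n = 15, SD proportional to mean: 1.3 / √(4.8020/15) = 2.298; Φ(0.338) = 63%.
- Equal SDs at other sizes: n = 17 gives 49%, n = 30 gives 73%, n = 36 gives 80%.

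**What repeat nights could do**

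Assume that 1.96 is the SD of a single trap-night, that each house is trapped on 20 nights (5 a month over January to April), and that a share ICC of the variance lies between houses. The document gives no ICC. The variance of a house mean is 3.8416 × (ICC + (1 − ICC)/20), so with 15 houses per arm:
- ICC 0.1: about 99.8% power.
- ICC 0.3: 3.8416 × 0.335 = 1.287; 1.3 / √(2 × 1.287/15) = 3.14; about 88%.
- ICC 0.5: 3.8416 × 0.525 = 2.017; 1.3 / √(2 × 2.017/15) = 2.51; about 71%.
- 80% requires ICC + (1 − ICC)/20 ≤ 15/35.68 = 0.420, so ICC must be below about 0.39. With unlimited nights the limit is about 0.42.

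If 1.96 is already a house-level SD, repeat nights add nothing and the 44% stands.

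**Sentinel house counts**

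30 per arm × 2 arms = 60 per country. That is 180 for three countries and 120 for two. Trial design {8} gives 120 without saying what it covers.

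**The case against.** The strongest defence is that the 44% describes a study nobody plans to run. It treats each house as a single observation, whereas light traps run five nights a month and the Statistical methods section analyses counts with mixed models for repeated measures within houses and villages. At a moderate ICC, 15 houses with 20 nights each could exceed 80%. This stands. A reader might infer from the arithmetic that the light-trap comparison is underpowered, or that its true power is 44%; the documents do not show that. Nor do they show the opposite: the ICC is unknown, it is not stated whether 1.96 is a per-night or a per-house SD, and over-dispersion could lower power further. The sample size section does not use the repeat nights, so they cannot support its 80%.

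Pooling three countries would give 45 houses per arm per technique and 88% power under Eq. 2. But the protocol sizes Zambia alone and copies the figure to Mozambique, and the Discussion speaks of three trials, so pooling is not the stated basis.

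Two further cautions are fair. That a variance was dropped is an inference, though the likeliest one: Poisson variances (18.1) or reading 1.96 as a variance (18.2) also come close to 17, but both contradict the stated SD. And 36 holds only for equal SDs; counts often vary less when their mean falls.

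A reader might also infer that traps and spray catches must be spread over all 30 houses. The documents do not require this. The endpoints section specifies fixed sentinel houses and keeps the two techniques apart, and Trial status says recruitment in Zambia and Mozambique ended in 2019.

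**Conclusion.** The stated 17 houses per arm is wrong under the protocol's own formula and inputs. Eq. 2 gives 36 with the stated SD in both arms, 23 to 27 if the spread falls in proportion to the mean, and never fewer than 18. The 15 light-trap houses per arm per country are fewer than any of these and fewer than 17 itself. On the basis of one value per house, they give about 44% power with equal SDs and 56% to 63% if the spread falls with the mean.

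The conclusion is limited to this: the calculation shown does not support 80% power. The power of the planned mixed-model analysis may be higher or lower than 80% and cannot be derived from the document. The mismatched house counts need reconciling, but the 120 has no bearing on power. This is a correction to a printed calculation for the entomological endpoint and leaves the clinical sample size untouched.

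**What to change.** - Replace 17 with the Eq. 2 result and state the SD assumed in each arm: 36 if both are 1.96, otherwise the figure for the assumption chosen.
- Say whether 1.96 is a per-night or a per-house SD.
- State the power available with 15 houses per technique per arm. Either give it on the Eq. 2 basis (44% with equal SDs), or recalculate with between-house and within-house variance and the planned number of trap-nights, shown over a range of ICC and SD.
- Correct the sum 17 + 12 = 30, and make the sentinel count in Trial design {8} agree with the 60 per country in Outcomes {12}, stating the unit.

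The cost is wording, a short recalculation and possibly a less favourable stated power. No change to the trapping layout, the number of houses or the number of trap-nights is required.

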#### Data collection and management

##### *Plans for assessment and collection of outcomes {18a}*

Study endpoints will include clinical, entomological, and cost-effectiveness data. Data will be collected electronically using Open Data Kit (ODK) software which was programmed and uploaded on mobile phones. Once households have been enrolled in the study, a household survey adapted from a WHO standardized Malaria Indicator Survey (MIS) questionnaire (Supplementary material 1) will be administered to capture baseline demographic, behavioral, and socio-economic household indicators. Each household will be assigned a unique identification code at the time of questionnaire administration.

Baseline household data will be collected between April and October, after the long rains in southern Africa.

Entomological sampling will be undertaken throughout the study period and initiated after the baseline socio-demographic household data collection. Clinical malaria baseline data will also be collected after the household baseline survey (November-April) and in subsequent malaria transmission seasons at similar time points after the intervention implementation (Fig. 2).

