### Statistical methods

#### Statistical methods for primary and secondary outcomes {20a}

A mixed-effects model will be used to compare clinical malaria incidence rates between the intervention and control arms, to allow for repeated measures within households, villages, and the effect of year. Possible confounders such as the age of child, gender, ethnicity, and season will be included in the models.

Differences in the abundance of mosquitoes caught indoors and outdoors will be made between the study aims to evaluate the impact of house screening on mosquito density. Mixed-effects models will be used to estimate differences in the numbers of mosquitoes, adjusting for repeated measures (i.e., within houses, villages), and other possible covariates such as the child’s age, gender, ethnicity, and rainfall. A Poisson distribution model with a log link function will be used, and a random factor for each data point will be included in the model to adjust for excess variation between data points (over-dispersion). All mean counts per treatment and their 95% confidence intervals (CIs) will be modeled as the exponential of the parameter estimates for models with no intercept included. No additional analysis will be conducted.

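### The entomological sample size rests on an assumed SD with no stated basis, and even on that SD the 15 light-trap houses per arm do not give the stated 80% power

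*Protocol article*

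**What the plan says.** The calculation is in the protocol article under Sample size {14}, Entomological. An earlier study in Nyimba "estimated that 2.6 *An. funestus* were caught using CDC light traps per night", and screening is expected to halve the indoor catch. The target is to detect this "with 80% power at the 5% level of significance". On variability the text says only: "As the standard deviation (SD) for this data was not reported, we assumed a SD of 1.96 for the sample size calculation". It then reports: "Using Eq. 2 below, we estimated that we would require 17 houses in each arm of the study". Eq. 2 is the usual two-means formula with a separate variance for each arm. The design has 30 sentinel houses per arm, 15 for light traps and 15 for spray catches. Mozambique takes the same size because no local mosquito data were available.

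Three other sections bear on what the SD should measure.

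- Entomological endpoints (Outcomes {12}) makes the primary entomological endpoint the mean catch per trap night by arm, and says: "Indoor host-seeking mosquitoes will be collected for 5 days each month using CDC UV light traps from 15 sentinel households".
- Statistical methods {20a} plans a log-link Poisson mixed model that allows for repeated measures within houses and villages, with a random term per observation for over-dispersion.
- Plans for assessment and collection of outcomes {18a} says: "Entomological sampling will be undertaken throughout the study period and initiated after the baseline socio-demographic household data collection".

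**The concern.** In Eq. 2 the SD enters as a square, so doubling it quadruples the houses needed. The mean and the effect size each have a stated origin. The SD has none, and no range is shown around it.

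The scale is also unclear. The 2.6 is a catch for one trap night. The endpoint averages several nights in the same fixed houses, and houses are the units that Eq. 2 counts. The relevant SD is therefore that of a house's mean catch, made up of true between-house variation plus whatever night-to-night variation remains after averaging. Nothing links 1.96 to that quantity.

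What is at stake is how the entomological result is read. If 80% power is believed, a non-significant difference may be taken as evidence against a 50% reduction when the comparison may have had much less power than that.

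**Working it through.** **Inputs**, all from Sample size {14}, Entomological: two-sided 5% level (z = 1.960), 80% power (z = 0.842), control mean 2.6, screened mean 1.3, difference 1.3, SD 1.96, 15 light-trap houses per arm. The text does not say whether 1.96 applies to one arm or both. The calculation is made per country, so these checks are too.

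**Attempt to reproduce 17.** Eq. 2 is n = (z_α/2 + z_β)² (σ0² + σ1²)/(μ0 − μ1)². Here (1.960 + 0.842)² = 7.849, 1.96² = 3.842 and 1.3² = 1.69.

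- Equal SDs of 1.96: 7.849 × 7.683 / 1.69 = 35.7, so 36 houses per arm.
- SD 1.96 in control and 0.98 in the screened arm: 7.849 × 4.802 / 1.69 = 22.3, so 23.
- One-sided 5%, equal SDs: 29.
- Near misses: one variance term only gives 17.8; reading 1.96 as a variance gives 18.2; Poisson variances 2.6 + 1.3 give 18.1. All three round up above 17.
- Solving Eq. 2 for n = 17 with equal SDs gives an SD of about 1.35.

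The printed 17 is not reproduced from the printed formula and SD.

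**Power at the stated SD.** Power = Φ(1.3/√((σ0² + σ1²)/n) − 1.96).

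| Houses per arm | Equal SDs 1.96 | SD 1.96 control, 0.98 screened |
|---|---|---|
| 15 (light-trap houses) | 44% | 63% |
| 17 (stated requirement) | 49% | – |
| 30 (all sentinel houses) | 73% | – |

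For 15 houses and equal SDs: √(7.683/15) = 0.716, 1.3/0.716 = 1.816, and Φ(1.816 − 1.96) = 0.44. With the SD halved: √(4.802/15) = 0.566, 1.3/0.566 = 2.298, and Φ(0.338) = 0.63.

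**Detectable difference with 15 houses, equal SDs 1.96:** 2.802 × 0.716 = 2.0 mosquitoes per night, or 2.0/2.6 = 77% of the control mean rather than 50%.

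**SD at which 15 houses do give 80% power:** (1.3/2.802) × √(15/2) = 1.27 with equal SDs, or (1.3/2.802) × √(15/1.25) = 1.6 in control if the SD halves with the mean.

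**Sensitivity to the SD.** The documents give no SD, so these variances are assumptions. Each is matched to its arm's mean, both terms of Eq. 2 are used, n = 15 per arm, and each house counts as one trap night.

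| Assumption | Variance, control + screened | Power |
|---|---|---|
| Poisson | 2.6 + 1.3 = 3.90 | 72% |
| CV 1 | 6.76 + 1.69 = 8.45 | 41% |
| Negative binomial, dispersion 1 | 9.36 + 2.99 = 12.35 | 30% |
| CV 1.5 | 15.21 + 3.80 = 19.01 | 21% |

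Averaging repeated nights raises these figures to the extent that the variation lies within houses. Variation between houses does not average out.

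**The case against.** The strongest reply is that the protocol is open about its assumption. Planning SDs are often assumed, and a journal article may leave the reasoning to the full protocol. This has some force: the missing rationale would be a small point if the power claim followed from the stated inputs. It does not follow, and the formula, the SD, the 17 and the 80% are all printed here.

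Three stronger readings are tempting, and the documents do not support them.

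- A reader might infer that 1.96 was carried over by mistake from the two-sided 5% normal quantile, which appears in the same formula. The match may suggest that but does not prove it. The text does not say how the value was chosen.
- A reader might infer that 1.96 is too small, because its variance of 3.84 is only about 1.5 times the Poisson variance of 2.6 while over-dispersion is expected. That comparison is for a single night. For a five-night house mean the Poisson variance is 2.6/5 = 0.52, and 3.84 is 7.4 times that. Averaging lowers the relevant SD and over-dispersion raises it, so the error could go either way.
- A reader might infer that one variance term was dropped, because that gives 17.8. This is one of several near misses, and power computed with one term is not the power of any two-arm comparison.

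It is also fair that the planned confidence intervals will show the precision achieved, and that clinical malaria, not mosquito density, is the trial's main outcome. Both points limit the weight of the finding. Neither makes the stated power correct.

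**Conclusion.** The point stands. The entomological sample size depends on an SD with no stated basis and no link to the between-house variation that the planned analysis faces. Taken at face value as a per-house SD, that value requires 36 houses per arm (23 if it halves in the screened arm) against the printed 17, and the 15 light-trap houses give about 44% (63%) power.

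These figures assume a normal approximation, one value per house, and a comparison within one country. They show that the stated 80% does not follow from the protocol's own inputs. They are not an estimate of the trial's actual power, and it would be wrong to conclude that the comparison is necessarily underpowered: with repeated nights and modest between-house variation it could reach 80% or more. The point is worth correcting but does not touch the primary clinical outcome.

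**What to change.** In Sample size {14}, Entomological, replace the 80% power statement with the power, or the detectable reduction, for 15 light-trap houses per arm. Show it over a stated range of SDs, use both variance terms of Eq. 2, and say what unit the SD describes. The sensitivity table above could serve, with a note that averaging repeated nights raises its figures.

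If light-trap catches were made in the sentinel houses before screening, use them, pooled across arms, to estimate between-house and within-house variation, and restate the power under the planned mixed model. The order of activities in {18a} makes such catches likely but does not establish that they exist or how many there are, and Zimbabwe was still recruiting according to Trial status. The sponsor should confirm this for each country. Pooling the arms avoids any treatment comparison.

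The cost is a short recalculation and an edit to one paragraph. No houses, trap nights or analyses are added. The only drawback is that the stated power may become less favourable.
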